#### Statistical methods to handle missing data

The groups will be analysed on an intention to treat basis. The analysis will determine effect sizes to conduct power calculations for a larger trial. In accordance with the intention to treat principles, our aim is to follow-up all participants regardless of whether they have been lost during the intervention. Any missing follow-up data will be modelled on the assumption that it is missing at random. Logistic regression will be used to test this assumption, and to calculate probability of providing complete outcome data with baseline variables as predictors. These analyses will be used to create inverse probability sampling weights for subsequent analyses on outcome.

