## Study aims and objectives

The study aims to culturally adapt and integrate two CBT approaches, MICBT and MBRP intervention for individuals with SUDs in Pakistan and to test the feasibility and acceptability of these interventions in a factorial RCT.

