#### Sample size

Based on the recommendations by Sim and Lewis [45], a minimum sample size of at least 50 participants per group is required for feasibility studies. Assuming 30% attrition rate, we aim to recruit a total of *N* = 260 participants, with 65 participants randomised to each arm according to 2 × 2 factorial design scheduled in given Table 2.

**Table 2 Tab2:** 2 × 2 Factorial design schedule of intervention with sample size

	TAU	MBRP	Total
MICBT	65	65	130
TAU	65	65	130
Total	130	130	260

The findings of this feasibility study will help determine the initial data for the outcome measures and will help in providing a sample size estimate for a larger future definitive trial; therefore, no formal power calculations have been undertaken.

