## Discussion

The protocol describes the process to assess the feasibility and acceptability of MICBT and MBRP (CAMIAB) intervention for individuals with SUD. Although these are evidence based interventions, research evidence on efficacy of these interventions for SUD in LMICs like Pakistan is limited. If proven effective, the trial will strengthen the evidence base for treatment of SUD. Based on the work during the trial period, we will establish a robust platform to conduct capacity building in order to facilitate opportunities for research knowledge deployment and knowledge exchange. It will also help shape clinical practice, government policy and research in relation to supporting individuals with SUD.

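### Effect sizes from this feasibility trial are too imprecise to be the target difference in the definitive trial's power calculation

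*Protocol article*

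**What the plan says.** The sentence at issue is in the protocol article under Statistical methods to handle missing data: "The analysis will determine effect sizes to conduct power calculations for a larger trial". The Sample size section says more loosely that the findings "will help in providing a sample size estimate for a larger future definitive trial". On this trial's own size it adds: "therefore, no formal power calculations have been undertaken".

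The size of this trial comes from a rule of thumb, that "a minimum sample size of at least 50 participants per group is required for feasibility studies". To this the section applies an allowance for loss: "Assuming 30% attrition rate, we aim to recruit a total of *N* = 260 participants". Table 2 in the same section puts 65 in every cell, so each factorial margin compares 130 with 130.

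The stated aim is "to test the feasibility and acceptability of these interventions in a factorial RCT". The Statistical analysis section describes a largely descriptive analysis centred on confidence intervals. The progression criteria under Primary outcomes are rates of recruitment, retention, attendance, adherence, attrition and assessment completion. The Discussion nevertheless says: "If proven effective, the trial will strengthen the evidence base for treatment of SUD". The matching sentence in the abstract depends on feasibility and acceptability instead.

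**The concern.** A power calculation needs a target difference and nuisance quantities such as the SD. A trial of this size estimates an SD fairly well and a treatment effect poorly. The required sample size varies with the inverse square of the target difference, so a modest error in the effect becomes a very large error in the size.

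If the observed effect becomes the target, chance largely decides how big the definitive trial is. An overestimate gives an underpowered trial. An underestimate gives one too large to run, and an estimate at or below zero gives no size at all.

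The Discussion sentence is a smaller matter. It holds out a conclusion on effectiveness that the stated aim does not include.

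**Working it through.** **The plan's own figure.** 50 × 1.30 = 65 per arm, and 4 × 65 = 260, so the stated total is reproduced by adding 30% to 50. Dividing by the expected retention would give 50/0.70 = 71.4, or 72 per arm and 288 in total. That is a separate point. What matters here is that 30% attrition leaves 65 × 0.70 = 45.5 per arm and 130 × 0.70 = 91 at each factorial margin.

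**Inputs.** From the Sample size section: 65 per arm, margins of 130 v 130, 30% attrition. Not given in the protocol, so assumed: SD = 1, two-sided 5%, 80% power for the later trial. The observed standardised difference d is shown at 0.30 and 0.50.

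**Formulas.** SE(d) = √(2/n + d²/(4n)); 95% CI = d ± 1.96 × SE; later size per group = 2 × (2.80/d)²; difference detectable with 80% power = 2.80 × √(2/n).

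**Pairwise, n = 45.5.** For d = 0.30, SE = √(0.04396 + 0.00049) = 0.211 and the half-width is 0.413.

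**Margin, n = 91, no interaction.** For d = 0.30, SE = √(0.02198 + 0.00025) = 0.149 and the half-width is 0.292.

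| Contrast | Observed d | 95% CI | Later size at d | Later size across the CI |
|---|---|---|---|---|
| Pairwise | 0.30 | -0.11 to 0.71 | 175 | 31 to no finite number |
| Pairwise | 0.50 | 0.08 to 0.92 | 63 | 19 to about 2,300 |
| Margin | 0.30 | 0.01 to 0.59 | 175 | 45 to effectively unbounded |
| Margin | 0.50 | 0.20 to 0.80 | 63 | 25 to 374 |

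Sizes are per group and use unrounded limits. For the third row the lower limit is 0.008, and 2 × (2.80/0.008)² = 245,000.

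**Detectable differences.** Pairwise: 2.80 × √(2/45.5) = 0.59 SD. Margin: 2.80 × √(2/91) = 0.42 SD.

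**Complete follow-up.** With 65 per arm, an observed 0.30 has an interval of -0.05 to 0.65. With 130 v 130 it is 0.06 to 0.54, which implies 53 to about 5,000 per group (2 × (2.80/0.544)² and 2 × (2.80/0.056)²). Better retention therefore does not remove the difficulty.

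**Consequence if the point estimate is the target.** This was simulated with 400,000 draws, a true d of 0.30 and the later trial planned for 90% power.
- The observed d was zero or negative in 8% of draws (pairwise) and 2% (margin).
- Among positive estimates, the central 80% of planned sizes was 63 to 2,138 per group (pairwise) and 87 to 1,337 (margin).
- Among the same estimates, the true power of the later trial was below 80% in 45% (pairwise) and 39% (margin).

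**Contrast with the SD.** There are 4 × 45.5 = 182 completers, giving 182 − 4 = 178 degrees of freedom. The 95% limits for the pooled SD are 0.906 and 1.116 times the estimate, about -9% to +12%. For a fixed difference in raw units, size varies with SD², so the error in size is 0.906² = 0.82 to 1.116² = 1.25, or -18% to +25%.

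No allowance is made for therapy groups of about eight or for the planned inverse probability weights. Both would probably widen the intervals for the effect.

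**The case against.** The strongest reply is that the sentence is loose rather than wrong. It does not say that the point estimate will be the target, or the only input. The Sample size section is compatible with using SDs, and the analysis centres on confidence intervals. That is fair, and the simulation describes only the most literal use. But the sentence names effect sizes as what the power calculation is to be conducted on. Using a confidence limit does not help either, since the lower limit gives an unworkable or infinite size.

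A second reply is that the factorial margin is the natural contrast and doubles the numbers. That stands, and it is why both contrasts are shown. It narrows the interval but leaves a half-width of 0.29 SD, and it needs the assumption of no interaction.

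Several stronger readings might be inferred, and the documents do not support them:
- **A biased decision to proceed or abandon.** The progression criteria are feasibility rates only. No rule makes progression depend on a large effect.
- **A contradiction with the absence of a power calculation.** That statement concerns this trial; the disputed sentence concerns the next one.
- **A failure to collect useful planning inputs.** Retention is already a primary indicator with a threshold, and detail on correlations or clustering may be left to the analysis plan.
- **A claim of efficacy.** The Discussion remark is one conditional sentence and changes no analysis.

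**Conclusion.** The concern holds for the one sentence in the missing-data section. On either contrast, following it as written gives an unreliable size for the definitive trial. The half-width is about 0.41 SD pairwise and 0.29 SD at the margin. An observed effect of 0.30 is compatible with later sizes from a few dozen per group to no usable number.

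These figures rest on a standardised scale, conventional alpha and power, the protocol's own attrition and, for the margin, no interaction. The general conclusion also survives complete follow-up. Nothing in this trial's conduct, sample size, outcomes or progression decision is affected; the harm falls on the planning of the next trial. The Discussion phrase is an inconsistency of wording with the aim and the abstract, and no more than that.

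**What to change.** Replace the sentence in the missing-data section with a statement along these lines: the definitive trial will be powered on a minimum important difference agreed in advance for its chosen primary outcome; this trial will supply the SD with its confidence limit, the baseline-outcome correlation and retention; any therapy-group intraclass correlation will be reported with its wide uncertainty; between-group differences will be reported with confidence intervals but will not be used as the target difference.

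In the Discussion, make the sentence conditional on the interventions being found feasible and acceptable, as the abstract already does.

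The cost is protocol wording, carried into the analysis plan. The Trial status section says recruitment has not begun, so the change is easy to make. The real work is that the team must choose a primary outcome for the later trial and agree a minimum important difference for it.

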### Data collection method

All participants (intervention and TAU groups) will undergo assessments at baseline, 3rd month (end of intervention) and at 6th month after randomisation. Participants will complete a self- report demographic information sheet (only at baseline) that will collect information related to age, duration of substance misuse, type of substance used etc., the MAP [47], SWEMWBS [42], EuroQoL (EQ-5D) [43] and CSRI [44]. All the assessments will be carried out by trained research assistants at baseline, 3rd month (end of intervention) and at 6th month.

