### Plans to promote participant retention and complete follow-up

Recruitment and retention are both an integral part of any drug and alcohol misuse trial due to the highly chaotic nature of this disorder. To increase retention of participants, protocols developed by Scott [48] will be used, where locater information will be recorded for each participant. Scott [48] achieved 95% retention of participants in his study on alcohol abuse. The study team will have regular contact with participants throughout the study period. Participants in the TAU group will be contacted by RA on weekly basis for first 3 months of the study to keep them engaged and retain in the study as well as to keep them well informed of the study’s progress. Both groups will be contacted monthly from 3 to 6 months to promote retention to the study. These contacts maybe done via a brief 5-min phone call.

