### Data analysis

#### Statistical analysis

The study data will be analysed using SPSS (Version-22). Analysis of data will take place after full recruitment and data collection. Descriptive data analysis will be performed to summarise demographic data and feasibility outcomes. Baseline and outcome assessment data will be summarised using the appropriate descriptive statistics and graphical summaries. As this is a feasibility study, the analysis of the data will be largely descriptive and will focus on confidence intervals for the difference amongst groups for each outcome measure. Possible between-group differences will be assessed using analysis of variance (ANOVA) and chi-square tests. The results of the trial will follow the standard CONSORT recommendations. A complete statistical analysis plan will be written prior to database lock and subsequently will be discussed and approved by the Trial Steering Committee (TSC). There is no interim analysis planned.

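### Logistic regression on baseline variables cannot test missing at random, and week-24 weights built from baseline variables alone ignore arm and the month-3 outcome

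*Protocol article*

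**What the plan says.** The protocol article, under *Statistical methods to handle missing data*, fixes three things in sequence.

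- The working assumption: "Any missing follow-up data will be modelled on the assumption that it is missing at random".
- How it is examined, and how response is modelled: "Logistic regression will be used to test this assumption, and to calculate probability of providing complete outcome data with baseline variables as predictors".
- What the model is for: "These analyses will be used to create inverse probability sampling weights for subsequent analyses on outcome".

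The same section gives the purpose of the outcome analysis: "The analysis will determine effect sizes to conduct power calculations for a larger trial".

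Four other sections bear on the point:

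- *Data collection method*: "All participants (intervention and TAU groups) will undergo assessments at baseline, 3rd month (end of intervention) and at 6th month after randomisation". A month-3 outcome will therefore exist for anyone lost between month 3 and month 6.
- *Sample size*: "Assuming 30% attrition rate, we aim to recruit a total of" 260. Attrition of 30% would leave 260 x 0.7 = 182 observed.
- *Plans to promote participant retention and complete follow-up*: "Participants in the TAU group will be contacted by RA on weekly basis for first 3 months of the study". The intervention arms have no matching weekly call in that period, although they do have weekly sessions.
- *Statistical analysis*: "Possible between-group differences will be assessed using analysis of variance (ANOVA) and chi-square tests". A complete analysis plan is promised before database lock.

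**The concern.** There are two linked problems.

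First, the stated test does not test what it is said to test. MAR says that, given the observed data, the chance of being observed does not depend on the unobserved value. A model of response on baseline variables has no unobserved value in it. A null result could be taken as reassurance about MAR, and a significant one as evidence against it. Neither reading is valid.

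Second, the only predictors named for the weights are baseline variables. In this population, dropout between month 3 and month 6 may well follow how a participant was doing at month 3, and contact in the first three months differs by arm. Weights that see neither arm nor the month-3 outcome cannot correct for dropout driven by them.

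At stake are the week-24 group differences and their confidence intervals, which are to supply effect sizes for sizing the definitive trial.

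**Working it through.** The plan gives no figure to reproduce. The only numerical input from the document is 30% attrition. Effect sizes, correlations and dropout slopes below are assumptions. Each simulation compares two arms, standing for one contrast among the four. Higher scores are worse, and the true week-24 effect is -0.30 SD.

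**Step 1. Can the model see a departure from MAR?**
MAR: P(R=1 | X, Y_obs, Y_mis) = P(R=1 | X, Y_obs). Planned model: logit P(R=1) = a + bX. Y_mis does not appear, so changing it cannot change b.

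Demonstration: dropout depends on arm and baseline, with retention 78% and 63%. All observed data are held fixed and only the unobserved week-24 values are shifted by delta. The weighted estimate uses baseline and arm.

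| delta | logistic coefficient | weighted estimate | true effect |
|---|---|---|---|
| 0 | -0.776 | -0.297 | -0.30 |
| 0.5 | -0.776 | -0.297 | -0.23 |
| 1.0 | -0.776 | -0.297 | -0.15 |

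The last column agrees with hand arithmetic. The missing fractions are 0.22 and 0.37, so the effect moves by (0.37 - 0.22) x delta = 0.15 x delta, giving -0.30, -0.225 and -0.15.

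**Step 2. How would the test behave at n = 260?**
Share of 1,000 simulated trials in which the baseline coefficient has p < 0.05:

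- missing completely at random: 5.5%
- MAR, odds ratio 2 per SD of the baseline variable: 99.8%
- not at random, driven by the part of the outcome unrelated to baseline, odds ratio 2: 5.0%

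The test rejects when MAR is true and stays silent when MAR is false. What it detects is dependence of dropout on baseline, which is evidence against missing completely at random.

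**Step 3. What do baseline-only weights leave uncorrected?**
Model: x ~ N(0,1); week 12 = 0.6x - 0.3(arm) + 0.8e; week 24 = 0.3x + 0.5(week 12) - 0.15(arm) + 0.7e. True effect = -0.15 - 0.5 x 0.3 = -0.30. Retention is about 70%, with 500,000 simulated participants.

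| Dropout depends on | baseline-only weights | baseline and week 12, each with arm interaction |
|---|---|---|
| arm alone | -0.30 | -0.30 |
| arm + baseline | -0.37 | -0.30 |
| arm x baseline | -0.53 | -0.30 |
| week-12 score, both arms | -0.26 | -0.29 |
| week-12 score, control arm only | -0.09 | -0.30 |
| unseen week-24 score, both arms | -0.26 | -0.28 |
| unseen week-24 score, control arm only | +0.02 | -0.13 |

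The last two rows are not-at-random mechanisms. Richer weights help there but do not remove the bias.

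**Step 4. Dropout near the planned rate, with retention differing by arm.**
TAU retention 80%, active arm 70%, log-odds of retention -0.8 per SD worse week-12 score:

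- Slope in the active arm only: baseline-only weights give about -0.39 to -0.46, an overstatement of 0.09/0.30 = 30% to 0.16/0.30 = 53%.
- Same slope in both arms: about -0.33 to -0.35, an overstatement of 10% to 17%.
- Same slope in both arms and 70% retention in both: -0.29 to -0.31, essentially no bias.
- A wider grid (baseline/week-12 correlation 0.3-0.7, week-12/week-24 correlation 0.4-0.8) extends the first two ranges to -0.48 and -0.36.
- In the first case, adding arm and week-12 score as main effects leaves about -0.37 to -0.44. Interactions with arm bring the estimate back to about -0.30.

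**Step 5. What this means for the next trial.**
Required sample size is proportional to 1/effect². If the true effect is -0.30 and the next trial is sized directly on the estimate, it would have (0.30/0.35)² = 73% of the participants it needs at -0.35, and (0.30/0.46)² = 43% at -0.46. At -0.26 it would have (0.30/0.26)² = 133%, that is, too many.

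**The case against.** The strongest reply is that this is a feasibility trial. Its primary outcomes and progression criteria (*Outcomes*) are recruitment, retention, attendance, adherence, attrition and completeness, and none uses these weights. Clinical measures are secondary and the analysis is described as largely descriptive. Nothing depends on the result of the supposed test, since MAR is assumed and the weights are built whatever it shows. This stands, and it limits the weight of the point. It does not make the sentence on testing correct, and the same section commits the analysis to supplying effect sizes for a larger trial.

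A second reply is that the article does not say baseline variables *only*, and that a later analysis plan may add predictors, interactions or sensitivity analyses. This is fair: the omission is read from what is named. But the article does name a predictor set for the weights, and as written that set is the wrong one for week 24. For week-12 outcomes the reply is stronger, because the month-3 value is then itself what is missing.

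Three stronger readings are tempting, and the document does not support them:

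- A reader might infer that any difference in dropout between arms biases the contrast. Dropout depending on arm alone does not (Step 3, first row).
- A reader might take a bias of around 50% as a property of the plan. It is the upper end of one assumed mechanism. Other mechanisms give little or no bias, or bias toward the null.
- A reader might infer that, fed into ANOVA and chi-square tests, the weights would act as case counts and inflate the sample. The article calls them sampling weights and does not say how variance is computed, so this cannot be held against it.

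**Conclusion.** The point holds in two parts.

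The statement that logistic regression on baseline variables tests MAR is wrong in principle. This rests on no assumption about the data.

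The weighting part is conditional. Week-24 weights built from baseline variables, as named, leave bias if dropout after month 3 depends on the month-3 outcome and the arms differ in that dependence or in retention. For an assumed true effect of -0.30 SD and 20-30% dropout, the estimate is about -0.33 to -0.35 when both arms are affected and -0.39 to -0.46 when only the active arm is. If the control arm is the one affected, the bias runs the other way. The document supplies only the 30% attrition figure, so these sizes are illustrations and not predictions.

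Severity is moderate: it should be fixed, but it does not threaten the feasibility conclusions.

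**What to change.** 1. Replace the statement that logistic regression will test the assumption with one saying that it will describe predictors of missingness. State that MAR is assumed and cannot be verified from the observed data.
2. Build the week-24 weights from baseline variables, arm, month-3 outcome, and interactions of the baseline and month-3 variables with arm, or fit them separately within arm. Use sessions attended only in the intervention arms, since TAU alone has none. A mixed model or multiple imputation with the same variables would serve equally well.
3. Use robust (sandwich) standard errors wherever the weights are applied.
4. Add one simple not-at-random sensitivity analysis, such as shifting the missing outcomes by a range of deltas, separately by arm. No weights built from observed data can cover that case.

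The cost is a change of wording and slightly more analysis, using only data already planned for collection. Richer weight models also give more variable weights, so their distribution should be reported. The article says recruitment has not begun and that the analysis plan is still to be written, so the change can be made now.

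### Regressing completeness on baseline variables cannot test missing at random, so the check named in the plan gives no evidence for or against the assumption behind the weighted effect sizes

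*Protocol article*

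**What the plan says.** The section Statistical methods to handle missing data sets out four steps.

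- The assumption: "Any missing follow-up data will be modelled on the assumption that it is missing at random".
- The check: "Logistic regression will be used to test this assumption". The only assumption the wording can point back to is missing at random, in the sentence before.
- The model: the same regression is used "to calculate probability of providing complete outcome data with baseline variables as predictors".
- The use of the model: "These analyses will be used to create inverse probability sampling weights for subsequent analyses on outcome".

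The section also says what the results are for: "The analysis will determine effect sizes to conduct power calculations for a larger trial". The Sample size section plans for 30% attrition. The Outcomes section makes the feasibility indicators primary. The scores on substance use, wellbeing and quality of life are secondary.

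**The concern.** Data are missing at random when, given what was observed, the chance of being missing does not depend on the unseen value. A regression of completeness on baseline variables contains no unseen value, so it cannot examine that condition. It shows only whether completeness varies with the baseline variables.

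Neither result can be read as a verdict on the assumption. A significant baseline predictor is compatible with missing at random and is what the weights are meant to handle. A null result is compatible with dropout driven by the outcome itself.

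At stake are the weighted effect sizes for the secondary outcomes, which are meant to power the larger trial. With about 30% missing, they rest on an assumption for which the named check supplies no evidence.

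**Working it through.** **1. What the regression estimates.** Let R = 1 if the outcome is observed, X the baseline variables and Y the follow-up outcome.

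- Missing completely at random (with respect to X and Y): P(R = 1 | X, Y) = P(R = 1).
- Missing at random: P(R = 1 | X, Y) = P(R = 1 | X).
- The planned regression estimates P(R = 1 | X) only.

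A slope on X contradicts the first line. The second line compares two quantities, and the regression supplies only the right-hand one. The left-hand one needs Y for participants whose Y is missing. Any fitted P(R = 1 | X) is therefore compatible with the second line being true or false.

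**2. Inputs from the documents.** The plan attaches no figure to this check. The simulations take 260 participants and 30% missing from the Sample size section. The 65 per arm there equals 50 × 1.30, and 4 × 65 = 260. Whether that is the right way to allow for attrition is a separate matter.

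**3. Inputs that are assumed.** The documents give no dropout mechanism, baseline-outcome correlation or SD. The outcome SD is set to 1. The log-odds of staying fall by a fixed slope per SD of the variable that drives dropout.

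**4. First set-up.** Five baseline variables; likelihood-ratio test of completeness on all five at the 5% level; then the inverse-probability-weighted mean; 1,000 trials per scenario.

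| Truth | Baseline-outcome correlation | Test significant | Bias of weighted pooled mean (SD) |
|---|---|---|---|
| At random (depends on a measured baseline variable) | – | 99.9% | about 0 |
| Not at random, slope 0.9 | 0 | 5.3% | −0.24 |
| Not at random, slope 0.9 | 0.2 | 12.2% | −0.23 |
| Not at random, slope 0.9 | 0.4 | 39.0% | −0.20 |

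With a slope of 0.3, the pooled-mean bias falls to about 0.07 to 0.08 SD.

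**5. Group differences in the same set-up (two groups, slope 0.9).** The Statistical analysis section focuses on differences among groups, so these matter more than the pooled mean.

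- Same mechanism in both groups, no true effect: bias about 0.00 SD at all three correlations.
- Same mechanism in both groups, assumed true difference 0.4 SD: the difference shrinks by about 0.05 SD.
- Outcome-driven dropout in one group only: bias about 0.23 to 0.25 SD.

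**6. Second set-up, as a cross-check.** One baseline variable correlated 0.5 with the outcome; 2,000 replicates; no true difference; weights from a logistic model with that variable and arm.

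| Truth | Baseline variable p < 0.05 | Bias after weighting (SD) |
|---|---|---|
| Completely at random | 5.2% | 0.00 (mean) |
| At random | 100% | 0.00 (mean) |
| Not at random, through the outcome itself (slope 0.8) | 75% | −0.16 (mean) |
| Not at random, through the part of the outcome that baseline does not predict (slope 0.9) | 5.2% | −0.18 (mean) |
| As the row above, in one arm only | 5.1% | −0.18 (difference) |

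**7. Reading.** The test was significant almost always when the assumption was true. When it was false, the test was significant in anything from 5% to 75% of trials, depending on how strongly baseline predicts the outcome. The significance rate reflects the link between completeness and baseline, not whether the assumption holds.

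**The case against.** The case on the other side has real force on consequences.

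- **No rule hangs on the test.** The section gives no threshold, no decision and no reporting statement, and the weights are built whatever the regression shows. Deleting the claim changes no planned estimate, and weighting under an assumed missing at random is a standard method. This stands. A reader might infer that results will be presented as if the assumption had been checked and passed; the documents do not say so.
- **Group differences are often spared.** If dropout depends on outcome in the same way in every arm, the weighted difference is nearly unbiased. This stands: a material bias needs a mechanism that differs by arm. The retention section describes weekly calls to the usual-care arm for the first three months, while the other arms attend sessions, so contact differs by arm. That makes such a mechanism possible but does not show it.
- **Relapse as the cause of dropout is not documented.** The retention section explains its effort as needed "due to the highly chaotic nature of this disorder", which concerns recruitment and retention in general. The eligibility criteria require completed detoxification but not recent detoxification. A reader might infer that relapse soon after detoxification will drive missingness; the text does not establish it. The protocol also plans locator information, regular contact and follow-up of participants who stop the intervention.
- **Sensitivity analyses can be left to the SAP.** This also stands: their absence from an article is not itself a fault. The fault is that the article names a check and the check is invalid. A sensitivity analysis is proposed here as its replacement.

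None of this makes the regression a test of missing at random.

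**Conclusion.** The statement that logistic regression on baseline variables will test missing at random is wrong as written. The conclusion follows from the definition of the assumption and does not depend on any simulated value.

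The size of the consequence does depend on assumptions. With 260 participants, about 30% missing and a slope of 0.9 per SD, bias in the weighted group difference ranges from about 0 (same dropout mechanism in all arms, no true effect) to about 0.23 to 0.25 SD (outcome-driven dropout in one arm only). Pooled-mean bias is about 0.07 to 0.24 SD for slopes from 0.3 to 0.9. These figures show what the check could miss; they do not predict what will happen in this trial.

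The point should be corrected but is of moderate weight. It bears on the secondary outcomes and on the effect sizes carried into the next trial. It leaves the primary feasibility outcomes and the progression criteria untouched. It would be too strong to say that the weighting is invalid or that weights can never help: in the first set-up, pooled-mean bias fell from 0.24 to 0.20 SD as the baseline-outcome correlation rose from 0 to 0.4.

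**What to change.** In Statistical methods to handle missing data, and in the SAP when it is written:

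1. Remove the claim in "Logistic regression will be used to test this assumption". Describe the regression as identifying baseline predictors of missingness and supplying the weights. It may be added that it can give evidence against missing completely at random.
2. State that missing at random is assumed given the variables in the weighting model, and that the observed data cannot test it.
3. In place of the invalid check, specify a delta-adjusted (tipping-point) sensitivity analysis of the secondary outcomes. Shift the values assumed for missing participants separately by arm, over a range fixed in advance (0 to 0.5 SD worse would be one example; the documents give no figure). Report the shift at which the conclusion about each group difference changes.

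The cost is a sentence or two of wording and some extra analysis on data already to be collected. Some estimates will look less certain. The article says recruitment has not begun and that the SAP will be written before database lock, so the change can be made in time.
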